### 2.2. Subjects and Eligibility

A total of 30 participants with MetS and prolonged daily eating duration will be enrolled in the study. The inclusion and exclusion criteria are described in Table 1.

Participants must have FPG of ≥100 mg/dL and two additional indicators of MetS, self-reported dietary intake of ≥14 h per day, regular daytime schedule of activity, self-reported habitual sleep duration of >6.5 h, and a smartphone with Apple operating system (OS) or Android OS [4]. We chose to use FPG as one of the necessary inclusion criteria of MetS diagnosis for several reasons. It is known that high FPG and T2D are common and associated with an increased risk of CVD and mortality [4,56]. High FPG is a prevalent component of MetS-component clusters which are frequent and have an increased cardiovascular risk [1,57,58,59]. Circadian rhythm disruption is associated with abnormal glucose metabolism and it was shown that TRE can improve glucose regulation and maintain blood glucose level within homeostatic range [10,11,12,13,30].

The exclusion criteria include diagnosis of diabetes mellitus, shift work, planned travel over time zones, recent history of major adverse cardiac events, other active or uncontrolled medical conditions, history of eating disorder or bariatric surgery, participation in the weight-management program, special or prescribed diet for other reasons, substance abuse, depression, sleep apnea, and treatment with antidepressants, medication affecting glucose metabolism or appetite, or immunosuppression.

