### 2.5. TRE Intervention

At Visit 3 (Week 3—intervention begins), participants will return to remove the CGM and review their mCC app data. Participants who are eligible based on blood work results and logging mCC app data will be subject to further steps of the trial. The food intake data from the baseline period will be downloaded from the server-side of the mCC app and the review of the data will be performed. Participants who satisfy logging criteria (recording ≥3 meals or beverages daily for at least 5 days a week) and have an eating interval of ≥14 h a day will undergo further approach. Participants who record <2 meals/day for >3 days or those with <6.5 h self-reported sleep for >3 days based on their data from the mCC app will be excluded from the study. The participants who meet the criteria for MetS (based on blood work results, BP, and/or waist circumference measurements), the mCC app logging criteria, and the BDI-II and ESS questionnaire criteria will be enrolled in the study (Table 1).

At Visit 3, participants will enter a 12-week monitored intervention between Weeks 3 and 15. Participants will meet with a dietitian in-person for behavioral nutritional counseling. At this visit, participants will be asked to restrict their food intake daily to 10 h a day and fast for 14 h. They will also be instructed to start the TRE intervention by selecting (together with study investigator) a 10-h eating window that best suits their lifestyle based on his/her baseline eating pattern from the first 2 weeks. This 10-h window must be between 7 a.m. and 9 p.m., with the last meal (including non-water beverage) consumed at least 2 h prior to the typical bedtime. The 10-h interval will be entered in the app, so participants can visualize their chosen daily eating window and consume all meals within this interval. Beverages that include caffeine or artificial sweeteners are not allowed outside of the 10-h feeding period, as some artificial sweeteners may affect glucose tolerance and caffeine can alter metabolism. Participants will also be able to modify the 10-h window based on their schedule; however, eating outside of the eating window by more than one hour more than twice per week is not allowed. TRE will be the only intervention, and participants will not be instructed to change their habits regarding physical activity or the quality, quantity, or caloric content of their diet.

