#### 2.6.3. Blood Samples

All participants will have their blood drawn at Visits 2, 5, and 7 in the morning after overnight fasting. Measurements of routine laboratory tests such as CMP including FPG, calcium, urea nitrogen, creatinine, sodium, potassium, chloride, total protein, serum albumin, bilirubin, alkaline phosphatase, aspartate aminotransferase, and alanine aminotransferase, as well as thyroid-stimulating hormone, glycated hemoglobin (HbA1c), and lipid profile including total cholesterol (TC), low-density lipoprotein (LDL)-cholesterol, high-density lipoprotein (HDL)-cholesterol, and triglycerides (TG), will be done in serum samples in a certified analytical laboratory.

Measurements of metabolic, neuroendocrine, inflammatory, and oxidative stress/antioxidant defense biomarkers other than listed above will be performed in the Department of Medical Biology and Biochemistry at the CM. Blood samples will be collected into polypropylene tubes (6 mL) without anticoagulant to obtain serum or in ethylenediamine tetraacetic acid (EDTA)-containing tubes (9 mL) to obtain plasma and erythrocytes. All samples will be centrifuged (6000× *g* for 10 min at 4 °C). The serum and plasma will be separated and stored at −80 °C for further analysis. Subsequently, the erythrocytes will be washed three times with phosphate-buffered saline (PBS) solution at a ratio of 1:3 with simultaneous centrifugation of the sample after each wash (6000× *g* for 10 min at 4 °C). The washed red blood cells will be mixed with a PBS solution to obtain erythrocytic suspension with a 50% hematocrit index. The suspension will be used to determine the parameters of oxidative stress.

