Changes in metabolic, neuroendocrine, inflammatory, and oxidative stress biomarkers measurements between Visits 2, 5, and 7 will be considered as the secondary outcome measures. Change in FPG measurements between Visits 2 and 5 will be considered as the main secondary outcome measure.

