The proportion of the total number of days recorded with the mCC app during the TRE monitored intervention period in which participants satisfied a requirement of a 10-h eating window will be used to quantify the adherence to TRE intervention. This proportion is considered as the primary outcome measure. Changes in eating window duration, defined as the duration from the first to last caloric intake over 24-h cycle collected via the mCC app, assessed at Visits 3, 5, and 7 will be considered as the secondary outcome measures. Changes in physical activity and sleep duration collected via the mCC app, assessed at Visits 3, 5, and 7 will be considered as the secondary outcome measures.

The food intake data (photo and/or annotation entries) will be downloaded from the server-side of the app and dietary analyses will be performed by a registered dietitian to calculate the overall calorie intake and estimated calories from macronutrient component [34]. Three-day food records from each study period (from baseline and the last 12 days of each phase of TRE intervention) will be randomly chosen and analyzed to characterize the macronutrient composition of the diet. Caloric estimates will be made using the Caloric King database. A dietitian will review the record with the participant to clarify potential omissions and ambiguities and to assure that additional information is provided to improve the accuracy of the macronutrient composition of the diet. Changes in calorie intake assessed at Visits 3, 5, and 7 will be considered as the secondary outcome measures. We note that a 3-day dietary intake protocol with no regard to whether the food intake occurs on weekdays or weekend may involve a limitation but is consistent with a protocol used by Wilkinson et al. [34] in the study of the US patients with MetS. Wilkinson et al. [34] indicated that their findings associated with an assessment of post-TRE calorie intake were consistent with other studies [25].

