The TREMNIOS trial will examine one group of 30 patients (pre-post TRE intervention) with no control group which is a potential limitation. This approach has been chosen given that this trial is a precursor for large-scale controlled trial in the future and available funding at this initial stage of study is limited which limits the overall number of patients. Following the results of power analysis, it is deemed advantageous to conduct a single arm trial with 30 participants rather than the controlled trial with a smaller sample size of each group. Whereas the evaluation of the adherence to the TRE intervention does not require a control group, the interpretation of exploratory data on cardiometabolic parameters will require caution. For example, because there is no control group, one cannot exclude the possibility that TRE-related changes in cardiometabolic parameters will be to some extent affected by the process of monitoring during the TRE intervention. The planned randomized controlled trial to be conducted after the TREMNIOS trial is expected to be free of this limitation. However, the lack of a control group in the TREMNIOS trial may limit the ability to predict the acceptability of participants to be randomized to intervention and control groups in a planned large-scale randomized-control trial.

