**Inclusion Criteria**
Age 18–75 years Body mass index ≥25 kg/m^2^ Metabolic syndrome defined as elevated fasting plasma glucose ≥100 mg/dL AND two or more of the following criteria increased waist circumference ≥102 cm in men, ≥88 cm in women elevated fasting plasma triglycerides ≥150 mg/dL (or on drug treatment for elevated triglycerides) reduced high-density lipoprotein (HDL)-cholesterol <40 mg/dL for men, <50 mg/dL for women (or drug treatment for reduced HDL-cholesterol) elevated blood pressure, systolic blood pressure ≥130 mm·Hg and/or diastolic blood pressure ≥85 mm·Hg (or drug treatment for hypertension) Own a Smartphone with Apple operating system (OS) or Android OS Average eating period ≥14 h/day Habitual sleep duration of >6.5 h If patients are on cardiovascular medications (such as lipid-modifying drugs including statins, over the counter drugs such as red yeast rice and fish oil, or anti-hypertensive drugs), no dose adjustments will be allowed during the study period

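### One Visit 2 FPG reading is both the entry gate and the baseline of a main secondary outcome, so the uncontrolled paired t-test leans towards an apparent FPG benefit

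*Protocol article*

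**What the plan says.** All from the protocol article:

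- **Gate.** Section 2.2: "Participants must have FPG of ≥100 mg/dL and two additional indicators of MetS". Table 1 makes FPG the compulsory component of the definition ("Metabolic syndrome defined as elevated fasting plasma glucose"), to which any two of four other components are added.
- **When the gate is applied.** Section 2.5, at Visit 3: "Participants who are eligible based on blood work results and logging mCC app data will be subject to further steps of the trial". The same section then enrols "The participants who meet the criteria for MetS (based on blood work results, BP, and/or waist circumference measurements"), together with the app-logging and questionnaire criteria.
- **Blood draws.** Section 2.6.3: "All participants will have their blood drawn at Visits 2, 5, and 7 in the morning after overnight fasting". Only one of these precedes the intervention.
- **Outcome.** Section 2.6.3: "Change in FPG measurements between Visits 2 and 5 will be considered as the main secondary outcome measure". Section 2.7 lists it with body weight as the two main secondary outcomes, and section 2.9 bases the sample size on these two.
- **Test.** Section 2.9: paired t-test of baseline against post-intervention value, two-tailed, 0.05. The trial has one arm.
- **Stated limitation.** The Discussion asks for caution with the cardiometabolic data and gives as its example that "TRE-related changes in cardiometabolic parameters will be to some extent affected by the process of monitoring during the TRE intervention". It does not mention regression to the mean.

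**The concern.** A single FPG reading is a person's usual level plus day-to-day and assay variation. When entry depends on that reading reaching 100 mg/dL, people who read high by chance are kept and people who read low by chance are lost. The mean Visit 2 value of those enrolled therefore overstates their usual level, and Visit 5 readings will on average be lower whether or not TRE works.

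A control arm selected in the same way would show the same fall and cancel it. Here the change is tested against zero, so the artefact counts as effect, always in the favourable direction. FPG is one of the two outcomes used to justify the sample size, and the Discussion says the results will inform the sample size and outcomes of the planned randomized trial. An inflated FPG change could carry into that design.

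**Working it through.** **Inputs from the article.** Cutoff 100 mg/dL; outcome Visit 5 minus Visit 2; paired t-test, two-sided 0.05, one arm; 26 analysed (section 2.9). I use 26 only as the number of pairs. The sample-size statement itself does not reproduce for a paired test: effect size 0.8 with 80% power needs 15 pairs, and 26 pairs give 97.5%. That is a separate matter and does not affect this check.

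**Assumed inputs (not in the article).** Screened mean μ = 100 to 110 mg/dL, between-person SD s_b = 8 to 10, within-person SD s_w = 4 to 6; normal distributions; no true TRE effect.

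**Formula.** With s_t = √(s_b² + s_w²) and z = (100 − μ)/s_t, the expected fall among those with Visit 2 FPG ≥ 100 is

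fall = (s_w²/s_t) × φ(z)/(1 − Φ(z)).

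*Largest case, μ = 100, s_b = 8, s_w = 6:* s_t = √(64 + 36) = 10; z = 0; φ(0)/0.5 = 0.798; fall = 3.6 × 0.798 = 2.87 mg/dL. The SD of change is 7.98, so the standardized shift is 2.87/7.98 = 0.36.

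*Smallest case, μ = 110, s_b = 8, s_w = 4:* s_t = √80 = 8.94; z = −1.118; ratio 0.246; fall = (16/8.94) × 0.246 = 0.44 mg/dL, standardized 0.08.

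**False-positive rate.** Simulated paired t-tests on 26 pairs with no TRE effect. The last column also drops Visit 2 values of 126 or more; the article excludes diagnosed diabetes but states no FPG ceiling, so 126 is my assumption.

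| μ / s_b / s_w | Null fall (mg/dL) | Two-sided false positives | Same, values ≥126 dropped |
|---|---|---|---|
| 100 / 8 / 6 | 2.87 | 42% | 2.79; 41% |
| 100 / 10 / 6 | 2.46 | 32% | 2.31; 29% |
| 100 / 8 / 5 | 2.11 | 34% | 2.08; 33% |
| 105 / 10 / 6 | 1.69 | 17% | 1.40; 13% |
| 105 / 10 / 5 | 1.20 | 14% | 1.01; 11% |
| 110 / 10 / 4 | 0.47 | 7% | 0.25; 5.6% |
| 110 / 8 / 4 | 0.44 | 7% | 0.29; 5.7% |

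Nearly all rejections are falls, for which the nominal rate is 2.5%. Against the planned effect size of 0.8, the artefact is 0.08/0.8 = 10% to 0.36/0.8 = 45%.

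**Is the dual use the cause?** Keeping the same gate but taking a fresh reading as baseline returns the false-positive rate to about 5% in all 18 combinations of μ (100, 105, 110), s_b (8, 10) and s_w (4, 5, 6).

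**Eating window, for comparison.** The baseline app log is used both to check the 14-hour criterion and as baseline. Assuming a mean of 13-15 h, between-person SD 0.75-1.5 h and day-to-day SD 1.5-2 h averaged over 14 days, the null shortening is 0.04-0.49 h. The intervention asks for about 14 − 10 = 4 h.

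**The case against.** **The outcome is exploratory and caution is already advised.** Adherence is primary and is not a change from a selected baseline. The Discussion's monitoring effect is given only as an example, and efficacy is left to a later trial. This stands and limits the weight of the point. But the general caution leaves the test and its 0.05 level in place, and this bias has a known direction and can be estimated.

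**The size is assumed.** True. With a screened population well above 100 mg/dL the bias almost vanishes; with a mean below 100 it exceeds the range given here.

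**Records are reviewed before Visit 2 (section 2.3).** No qualifying FPG is specified there. Had an earlier reading of at least 100 also been required, the 100/8/6 case would drop to a fall of 1.98 mg/dL, with 23% falsely significant falls. That is smaller, but not nil.

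**Section 2.6.4 speaks of enrolment at Visit 2.** Section 2.5 still applies the blood-work gate at Visit 3.

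**Stronger readings that the article does not support.** A reader might infer that triglycerides, HDL and blood pressure are equally affected. They are any two of four components including waist, drug treatment can satisfy each of these three, and blood pressure is a mean of three readings, so the effect is weaker. A reader might put eating window ("Changes in eating window duration, defined as the duration from the first to last caloric intake over 24-h cycle collected via the mCC app") on a par with FPG; the shift is under half an hour against about four hours, so no conclusion turns on it. Nor does it follow that any observed FPG fall would be an artefact, only that part of it may be.

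**Conclusion.** The point holds for FPG. Sections 2.2, 2.5, 2.6.3 and 2.9, read together, make one noisy and compulsory reading both gate and baseline for an uncontrolled paired test. The direction of the bias follows from the design. Its size rests on the assumed mean and SDs: about 0.4-2.9 mg/dL, with false-positive rates of about 7-42%, or about 5.6-41% if values of 126 or more are also excluded. The primary outcome is untouched. This should be corrected before analysis, but it does not undermine the trial's feasibility aim.

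**What to change.** 1. Keep FPG change as a main secondary outcome, but state that a benefit will be claimed only if the change in CGM mean fasting glucose agrees in direction and significance. That measure is already a secondary outcome and is not used for selection. State the days over which it is averaged, since section 2.6.2 labels it by visit while the sensor is worn for two weeks.
2. Report the observed FPG change beside the expected null shift from the formula above. Take the mean and total SD from the Visit 2 FPG of everyone who had that draw, including those then excluded, and use a range of within-person SDs. The Visit 5 to Visit 7 variation (SD of the difference divided by √2) can serve as an upper guide, because it may include true change over the self-directed phase.
3. Name regression to the mean in the Discussion's limitations.

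Cost: a stricter rule for claiming benefit and a little more analysis, with no new samples or visits. One weakness remains: CGM wear starts at Visit 2, so glucose deviations lasting days may carry partly into its baseline. It is corroboration and does not fully replace an independent baseline.

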#### 2.6.4. myCircadianClock Application

The mCC app is a free smartphone application that was developed at the Salk Institute for Biological Studies, La Jolla, CA 92037, USA [25]. [name] and [name] from the Salk Institute, who are also members of the research team of this study, are the administrators of data collected on the server using this application.

The mCC app will serve as an electronic food, activity, and sleep diary. During the TRE intervention, data from the mCC app will be used to assess participant adherence, eating window, physical activity, and sleep. The mCC app is designed to run on Android and iOS devices and uses HIPAA compliant Amazon Web Server for server-side operations. A dedicated team of developers makes periodic updates to the app and to the backend server to comply with updates released by Apple, Google, and Amazon. The server side is designed to run multiple independent studies and the app is designed for individual customization. This allows study-specific customization by the investigator and user-specific customizations by participants.

For the TREMNIOS clinical trial, the mCC app was customized to be used in a single group assignment (TRE intervention group) study. After the enrollment of participants at Visit 2, the study investigator will generate a unique activation code. During the 2-week baseline period, participants will be asked to log their habitual food intake, physical activity, and sleep. Participants will not receive unsolicited feedback from the study investigators or the mCC app during baseline. At Visit 3, subjects will self-select a 10-h interval for consuming all of their food and beverages during the TRE intervention. Their chosen eating interval is highlighted in the app so that they can easily track the progress of their daily eating within their set interval. Participants will be asked to log all food intake, physical activity, and sleep quantity/quality every day for the baseline period and for the duration of the TRE intervention between Visits 3 and 7 (Figure 1). Other details regarding the use of the mCC app during the TRE intervention are included in Section 2.5.

On the server-side, a sub-study dashboard was created for this clinical trial. In the study summary dashboard, the participant’s study code, and the date of activation of the app will be shown along with their daily logs in real-time. The designated members of the research team will have password-protected access to the real-time data, will log in to the dashboard at least twice weekly to monitor food intake data, and perform real-time tracking of TRE adherence, and follow up participants with inconsistent logging as necessary. If participants do not log or show inconsistent logging for two or more days, they will be contacted by telephone, and app users will be reinforced. Logging adherence will be determined by a minimum of two caloric entries >5 h apart for a given day. Adherence to the designated eating window implies that all caloric items were contained within a 15-min buffer on each side of the self-selected 10-h eating window. The time-stamped food data is also shown as a “feedogram” raster plot along with the eating duration for each day. This will offer a visual summary of the participant’s eating pattern. The protocol of this study has an app-based component allowing for real time tracking of adherence and correlating glucose levels with food intake.

The results from previous TRE studies which used mCC app [25,34,35] have demonstrated that adherence to mCC app use is high, mainly due to the simplicity of logging food metadata. The mCC app takes ~10 s for logging one meal by using the picture feature. If, for any reason, the participant does not wish to record a picture of food item(s), there will be also an option to enter the name of food in Polish or English (by choosing the name of food from the list) and the approximate time that food was consumed. Because a Polish version of mCC app is not available, we will provide participants with the list of common food with the names both in Polish and English. We will also provide the participants with required support regarding the use of mCC app, including special app training at Visits 1, 2, and 5. If a participant faces difficulty logging data or has questions about the app, he/she will be able to contact the study investigator through the feedback feature of the app. Although self-reporting of adherence by patients is generally not accurate, it was shown that the false-negative rate (i.e., food consumed but not logged) using the mCC app is ~10% [25,61].

The proportion of the total number of days recorded with the mCC app during the TRE monitored intervention period in which participants satisfied a requirement of a 10-h eating window will be used to quantify the adherence to TRE intervention. This proportion is considered as the primary outcome measure. Changes in eating window duration, defined as the duration from the first to last caloric intake over 24-h cycle collected via the mCC app, assessed at Visits 3, 5, and 7 will be considered as the secondary outcome measures. Changes in physical activity and sleep duration collected via the mCC app, assessed at Visits 3, 5, and 7 will be considered as the secondary outcome measures.

The food intake data (photo and/or annotation entries) will be downloaded from the server-side of the app and dietary analyses will be performed by a registered dietitian to calculate the overall calorie intake and estimated calories from macronutrient component [34]. Three-day food records from each study period (from baseline and the last 12 days of each phase of TRE intervention) will be randomly chosen and analyzed to characterize the macronutrient composition of the diet. Caloric estimates will be made using the Caloric King database. A dietitian will review the record with the participant to clarify potential omissions and ambiguities and to assure that additional information is provided to improve the accuracy of the macronutrient composition of the diet. Changes in calorie intake assessed at Visits 3, 5, and 7 will be considered as the secondary outcome measures. We note that a 3-day dietary intake protocol with no regard to whether the food intake occurs on weekdays or weekend may involve a limitation but is consistent with a protocol used by Wilkinson et al. [34] in the study of the US patients with MetS. Wilkinson et al. [34] indicated that their findings associated with an assessment of post-TRE calorie intake were consistent with other studies [25].

